## 2. Materials and Methods

### 2.1. Study Design and Participant Recruitment

This study will be a randomized control trial. The study will consist of two groups: one sport-event group (SG) and one control group (CG); see Figure 1.

Sample sizes were calculated using G*Power 3.1 software (Heinrich-Heine-University Dusseldorf, Dusseldorf, Germany). Calculations were based on a previous study [7], and we aimed to achieve a substantial effect size of 0.8 (Cohen’s d) on blood biomarkers. With an alpha of 0.05 and a power of 80%, 40 participants (20 participants per group) are required to achieve a robust estimation of the relevant parameters. All participants will be required to be over 18 years of age to participate in the study. Prior to data collection, all participants will be fully familiarized with testing procedures and the laboratory environment. In addition, a pilot study will be performed prior to actual experimental data collection. This will provide valuable information concerning timing, standardization, subject preparation, data collection information, logistics, and experimental organization in terms of data management for all participants pre- and post-testing. Members of the research team supervising each different aspect of data collection will ensure the standardization and integrity of data collection. Blood samples will be collected at several phlebotomy locations to ensure bloodletting is performed immediately post-match. There will also be several locations provided by the research team to collect biomechanical and cognitive-motor task data. These multiple locations will enable efficiency and effectiveness in data collection post-event, minimizing the effect of time as a confounding variable.

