All the recruited participants will be male rugby 7 s players based at Cardiff Metropolitan University. Inclusion criteria will be participation in rugby 7 s tournaments for a minimum of 2 years and free from injury. After agreeing to participate in this study and passing the eligibility assessment, the participants will sign informed consent forms outlining the experimental design and procedures and will then be randomly assigned to SG or CG in a ratio of 1:1. The control group will comprise 7 s rugby players who are part of the 7 s squad but will not be participating in the actual rugby competition. Therefore, they will be injury- and fatigue-free, and direct comparisons will be possible to investigate the effect of games and contact on sports performance. In addition, baseline measures will also be useful in determining any changes within and between groups. This will enable meaningful comparisons between groups that are sport-specific. Both groups will participate in baseline and post-match data collection. Randomization will be conducted using the random function available in Excel software. All participants will be asked to maintain their regular training and dietary habits during the testing period. The participants will also be required to record their exercises and food intake for 24 h prior to each blood sampling. 

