#### 2.2.2. Blood Methodology

Prior to the competition (the day before), 10 mL of blood will be collected from each player into two separate 5 mL serum separation vacutainer tubes (SSTs) (Becton Dickinson, Rutherford, NJ, USA). These samples will be collected at the same time of day to avoid diurnal effects. Consistency in timing, data collection, and standardization of experimental testing will also provide experimental rigidity and will be established using results from a pilot study prior to data collection.

On competition day, a 10 mL blood sample will be collected into two separate 5 mL SSTs prior to the first rugby game and then again immediately after each subsequent match. Following the final rugby match, blood will be immediately collected, in addition to further sampling at 24 h, 48 h, and 72 h later, also using two separate 5 mL SSTs. All blood samples will be taken using the venipuncture method. Blood will be collected and left to coagulate at room temperature for one hour. After incubation, the blood will be centrifuged at 1250× *g* for 10 min at 4 °C. On completion of centrifugation, the serum supernatant will be collected and kept at −80 °C in two tubes (Eppendorf^®^). Two separate Eppendorf tubes are a requirement, because the serum from both 5 mL SSTs will be kept at Cardiff Metropolitan University for analysis. One tube will facilitate the analysis of serum creatine kinase (CK), cardiac troponin T, and cortisol, while the serum from the other 5 mL SST will be used for the analysis of serum neuron-specific enolase (NSE), protein S100B (S100B), brain-derived neurotrophic factor (BDNF), glial fibrillary acidic protein (GFAP), and ubiquitin carboxyl-terminal esterase L1 (UCHL1). Keeping two separate vials will prevent freeze-thaw cycles and therefore maintain the integrity of the serum samples.

Serum NSE, cardiac troponin T, S100-B, and cortisol will all be measured by an electrochemiluminescence immunoassay using a Modular Analytics E analyzer, supplied by Roche Diagnostics; serum CK will be measured using a Specord 200 spectrophotometer with a Roche/Hitachi 917/MODULAR P analyzer; and BDNF, GFAP, and UCHL1 will be analyzed using an enzyme-linked immunosorbent assay (ELISA).

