### 2.5. Statistical Analysis

Data will be analyzed using IBM SPSS 26.0. Diagnostic testing (e.g., outlier detection, distribution examination, homogeneity checking) will be conducted for all data, and all skewed values and missing values will be addressed using a multiple imputation approach. To examine the differences between the baseline and the testing days for each of the physiological, cognitive-motor, and whole-body movement skills, a series of generalized linear mixed models will be employed, controlling for several demographic covariates. Post hoc tests will be performed using the Bonferroni procedure, Mann-Whitney U test, and Chi-square test for different types of data. The significance level will be set at 95% (two-tailed). The effect size of Cohen’s d will be calculated, with 0.3, 0.5, and 0.8 indicating small, medium, and large effect sizes, respectively.

Due to the difference in the type of data (discrete and continuous), a variety of methods will be employed, including statistical parameter mapping to examine continuous data between the four sessions and baseline. A canonical analysis will be used as a multivariate technique to determine the relationships between the variables and the selected performance of key dependent variables. All collected data will be anonymized and stored on a password-protected computer, with access only granted to the lead investigator.

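### Section 2.5 states its main contrast as testing sessions against baseline and names no comparison of the randomised groups, so the stated test does not separate play from practice, retest or time-of-day effects

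*Protocol article*

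**What the plan says.** Section 2.1 of the protocol article describes a randomised trial in which players "will then be randomly assigned to SG or CG in a ratio of 1:1". Both groups attend baseline and post-match testing, and the section says of the design: "This will enable meaningful comparisons between groups that are sport-specific". The sample size is 20 players per group for a Cohen's d of 0.8.

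Section 2.5 describes the analysis differently. The purpose of the models is "To examine the differences between the baseline and the testing days for each of the physiological, cognitive-motor, and whole-body movement skills", and for this "a series of generalized linear mixed models will be employed, controlling for several demographic covariates". Waveform data are handled by "statistical parameter mapping to examine continuous data between the four sessions and baseline". The follow-up tests are described thus: "Post hoc tests will be performed using the Bonferroni procedure, Mann-Whitney U test, and Chi-square test for different types of data". The section does not mention SG, CG or a group-by-session term, and it does not say which factor the post hoc tests compare.

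**The concern.** A change from baseline to a later session contains everything that changes with time, not only the effect of playing. Section 2.1 schedules the battery at baseline, after each of three games, and at 24, 48 and 72 h. That makes six retests within a few days, so some learning is plausible. Section 2.2.2 draws blood before the first game and after each match, so match-day samples necessarily fall at different clock times. This matters most for cortisol. The control group is there to remove such shared drift, but it does so only if the test compares the groups.

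The Discussion adds to the difficulty, because it expects declines over the repeated sessions and attributes them to fatigue or a concussive event. A baseline-to-session change cannot support that attribution by itself. Shared drift could be credited to play, or a learning gain could offset a real decline.

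**Working it through.** **1. The plan's own figure.** Section 2.1 gives d = 0.8, alpha 0.05, power 80% and 20 per group. A two-sample t-test needs 20.03 per group one-sided and 25.5 per group two-sided. With 20 per group the two-sided power is 69%. The stated number is therefore that of a two-group comparison, and it agrees with a one-sided test only. Sidedness is a separate point. What matters here is that the trial was sized on the contrast that Section 2.5 does not name.

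**2. Inputs for the illustration.** The document gives neither the size of any drift nor the baseline-to-retest correlation (rho) of the outcomes. Both are assumptions: drift 0.1 to 0.5 SD, equal in both groups, and rho 0.4 to 0.7. The only reliability figures in the document are 0.58 and 0.40, quoted in the Introduction for SAC and mBESS.

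**3. Rejection rate with drift and no rugby effect.** The SD of a change score is SD × √(2(1 − rho)), so the standardised shift is dz = drift / √(2(1 − rho)). For example, drift 0.3 and rho 0.5 give dz = 0.3 / √1 = 0.30. The power of a two-sided 5% paired t-test at dz is then the rate of significant session effects. Section 2.5 does not say whether the session effect is taken in SG alone or over both groups, so both are shown (SG alone, n = 20 / both groups pooled, n = 40):

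| Drift (SD) | rho 0.4 | rho 0.5 | rho 0.7 |
|---|---|---|---|
| 0.1 | 7% / 9% | 7% / 9% | 9% / 13% |
| 0.2 | 12% / 20% | 14% / 23% | 20% / 36% |
| 0.3 | 21% / 39% | 25% / 46% | 38% / 67% |
| 0.5 | 49% / 80% | 56% / 87% | 78% / 98% |

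In the SG-CG difference in change the common drift cancels. A simulation of 20,000 trials at rho 0.5 and 0.7 gave about 5% throughout.

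**4. Masking.** Suppose play truly lowers a score by 0.8 SD and practice raises it by 0.3 SD in both groups.
- Within SG: −0.8 + 0.3 = −0.50.
- Pooled over groups: (−0.50 + 0.30) / 2 = −0.10.
- SG minus CG: −0.50 − 0.30 = −0.80.

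Only the group contrast recovers the effect. In the same simulation the pooled session test was significant in only 7% to 8% of trials.

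**5. Power of the group contrast at 20 per group.** Adjusting for the baseline value reduces the residual SD to SD × √(1 − rho²), so the effective size is 0.8 / √(1 − rho²). This is 0.873, 0.924 and 1.120 at rho 0.4, 0.5 and 0.7. Two-sided t-test power:

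| | rho 0.4 | rho 0.5 | rho 0.7 |
|---|---|---|---|
| One contrast, alpha 0.05 | 77% | 81% | 93% |
| Bonferroni over six sessions, alpha 0.05/6 | 50% | 56% | 77% |

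**The case against.** The strongest reply is that silence is not exclusion. Section 2.5 names a purpose and a model class and does not list the model terms, which a condensed article may leave to a fuller plan. Section 2.1 expects changes within and between groups. Mann-Whitney U is an independent-samples test, and SG versus CG is the only independent grouping that the design defines. A reader might infer from Section 2.5 that the randomised control is not used at all. The document does not support that, because a group comparison may well be intended.

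There are also mitigations. Participants are to be fully familiarised with the tests beforehand, and competition-day blood includes a sample before the first game. Section 2.2.2 says of the day-before draws: "These samples will be collected at the same time of day to avoid diurnal effects". These measures reduce the problem only in part. Familiarisation cannot be assumed to remove learning over six retests, and samples after successive matches cannot share one clock time.

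A second tempting reading is that drift will mainly produce false effects of rugby. For cognitive-motor tasks this is doubtful. Practice usually improves scores while the hypothesis is a decline, so masking is the likelier error there. Nor does the document support any particular drift in markers such as CK, S100B or GFAP.

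What remains is that Section 2.5 does not leave the contrast open. It states one, for the models and again for the parameter mapping, and it is not the randomised one.

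**Conclusion.** The point stands in this form: the stated contrast is sessions against baseline, and the SG-CG contrast that the design, sizing and Section 2.1 all imply is not named. Followed as written, the test mixes the effect of play with shared time effects, and the bias can have either sign.

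The figures of 7% to 78% within SG and 9% to 98% pooled illustrate the range under the assumed drifts and correlations; they are not estimates for this trial. With small drift the inflation is slight. The conclusion about which contrast to use does not depend on the assumed values, because a drift shared by both groups cancels in the group contrast whatever its size.

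**What to change.** For each outcome, state in Section 2.5 a mixed model with group, session, group-by-session, the player's own baseline value as a covariate (or baseline means constrained equal) and a random player effect. Name the SG-CG difference at one stated key session, or averaged over sessions, as the main result. Adjust the other sessions by Bonferroni and report within-SG changes as descriptive. Use the same group contrast in the parameter mapping, and say which groups the Mann-Whitney U and Chi-square tests compare.

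Choosing a single main contrast matters, because Bonferroni over all six sessions costs much of the power shown above.

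The cost is small. Both groups already attend baseline and post-match collection, so the analysis change is rewording. The one practical item is to confirm that CG sessions are held at the same clock times as SG sessions, which is a scheduling matter and not only wording.

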Baseline testing will include measures of (1) demographics, (2) blood, and (3) biomechanical and cognitive-motor tasks and will be conducted on the day before the tournament. The information on the tournament play of each participant in SC, i.e., approximate playing time, number of matches played, and time that the last match was finished, will be recorded and used as the time markers of post-match testing. Post-match testing, including blood and biomechanical and cognitive-motor tasks, will be performed immediately after each game and three times after the third game at 24, 48, and 72 h (Figure 1, Table 1). All data will be collected at the Human Performance Laboratory at Cardiff Metropolitan University. The same order of testing will be standardized for all players based on pilot study results. All experimental data collection will take place immediately post-game for all three matches. Players will report to the laboratory located pitch side for all blood, biomechanical, and cognitive data collection. Once data collection has finished, players will be told to shower and relax. The players will then be asked to return to the laboratory at 24, 48, and 72 h after the tournaments for repeated blood measurements and biomechanical and cognitive-motor tasks. There will be no physical activity during this post-activity testing period.

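### Section 2.5 adjusts only for demographics and uses baseline as a comparison session; if the groups are compared on change from baseline, adjusting for each outcome's own baseline would be more precise at the same 40 players

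*Protocol article*

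**What the plan says.** Players "will then be randomly assigned to SG or CG in a ratio of 1:1" (section 2.1). The same section states "Both groups will participate in baseline and post-match data collection" and "Baseline testing will include measures of (1) demographics, (2) blood, and (3) biomechanical and cognitive-motor tasks". Its declared purpose for these data is that "baseline measures will also be useful in determining any changes within and between groups".

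The analysis is in section 2.5. Baseline and testing days are to be contrasted for each type of outcome, and for this "a series of generalized linear mixed models will be employed, controlling for several demographic covariates". Demographics are the only class of covariate named. Baseline appears as the session of reference. The section writes down no group term and no group-by-session term. It also sets the test level: "The significance level will be set at 95% (two-tailed").

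On size, section 2.1 says "we aimed to achieve a substantial effect size of 0.8 (Cohen’s d) on blood biomarkers" and "With an alpha of 0.05 and a power of 80%, 40 participants (20 participants per group) are required". It gives neither sidedness, nor a baseline to post-match correlation, nor the SD to which d refers.

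**The concern.** With 20 players per group, a player's own baseline will often predict his post-match value better than his demographics do. The design collects that value in both groups, but section 2.5 does not use it as a covariate. If baseline is simply one level of the session factor and the two groups' baseline means are estimated freely, the group comparison at a post-match session is a difference in change from baseline. That fixes the coefficient on baseline at 1. Adjustment estimates the coefficient from the data.

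Only precision is at stake. When ρ is low, subtracting baseline adds noise, and the change comparison can be less precise than ignoring baseline altogether. When ρ is high, the two approaches nearly coincide.

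**Working it through.** **Inputs.** From the article: d = 0.8, alpha 0.05, 80% power, 20 per group (section 2.1); two-tailed testing (section 2.5). Assumed, because the article does not give them: ρ; the SD behind d; equal SDs at baseline and post-match; a roughly normal outcome; one post-match session.

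**Step 1: the plan's own figure.** By the normal approximation, n per group = 2(z_α + z_β)²/d².
- One-sided: 2(1.645 + 0.842)²/0.64 = 19.3, so 20 per group. This matches the stated 40.
- Two-sided: 2(1.960 + 0.842)²/0.64 = 24.5, so 25 per group.

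With the exact noncentral t, 20 per group gives 79.9% power one-sided and 69.3% two-sided. The stated 80% therefore fits a one-sided test.

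**Step 2: variances.** Set the SD of a single measurement to 1.
- Post-match value alone: 1.
- Change from baseline: 2(1 − ρ).
- Baseline-adjusted: 1 − ρ².
- Ratio of adjusted to change: (1 − ρ²)/[2(1 − ρ)] = (1 + ρ)/2, which is below 1 for every ρ < 1. At ρ = 0.5 it is 0.75.

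**Step 3: power if d = 0.8 is on the post-match SD.** The noncentrality is (0.8/√variance) × √(20/2), with 38 df for change and 37 for adjustment. Example at ρ = 0.5: change 0.8/√1 × √10 = 2.53, power 69.3%; adjusted 0.8/√0.75 × √10 = 2.92, power 81.2%.

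| ρ (assumed) | Change | Baseline-adjusted | Gain (points) |
|---|---|---|---|
| 0.3 | 54.9% | 73.3% | 18.4 |
| 0.4 | 61.4% | 76.7% | 15.3 |
| 0.5 | 69.3% | 81.2% | 11.9 |
| 0.6 | 78.7% | 86.8% | 8.1 |
| 0.7 | 88.9% | 93.2% | 4.3 |
| 0.8 | 97.4% | 98.4% | 1.0 |

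Comparing post-match values alone gives 69.3% at any ρ, so below ρ = 0.5 the change comparison does worse than ignoring baseline. Adjustment reaches 80% at ρ of about 0.48. The formula is slightly favourable to adjustment: a simulation of 100,000 datasets at ρ = 0.5 gave 69.3% for change and 80.1% for adjustment.

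**Step 4: power if d = 0.8 is on the SD of the change.** The change comparison then has 69.3% at any ρ. The adjusted effect size is 0.8/√[(1 + ρ)/2], which gives 86.3% at ρ = 0.3, 81.2% at 0.5, 76.2% at 0.7 and 73.8% at 0.8.

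**Step 5: more than one session.** Suppose the effect is 0.8 at each of three post-match sessions and all sessions are equally correlated. For their average, change versus adjusted is 72.3% versus 95.9% at ρ = 0.3, 85.5% versus 96.8% at 0.5, and 97.4% versus 99.3% at 0.7. The levels rise and the order stays the same.

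**The case against.** The strongest reply is that section 2.5 is a condensed paragraph in a journal article. How baseline enters a mixed model is often settled in an analysis plan, and naming demographic covariates does not exclude others. Nothing says that the groups' baseline means are estimated freely. A mixed model with baseline as one session is even compatible with a common baseline mean, which is one of the remedies below. This stands in part, and it is why the point is conditional: the change contrast is inferred from section 2.1, because no group-by-session term is written. It does not remove the point, because section 2.5 does name its class of covariates and gives baseline a different role.

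A second reply is that the benefit depends on unknowns. This stands. At ρ = 0.8 the gain is about 1 point, and the pattern across ρ reverses when d is put on the change SD. The only correlations in the article are reliability coefficients in the Introduction: 0.40 for mBESS and 0.58 for SAC. They are not biomarker correlations, and the sizing concerns biomarkers. They show only that values in the range of large gains are plausible for at least one listed outcome, the mBESS.

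Four stronger readings may tempt a reader, and the article supports none of them:
- *The missing adjustment is why power is 69% instead of 80%.* It is not. That gap comes from sizing that fits a one-sided test set against a two-tailed analysis.
- *Adjustment restores 80%.* On the post-match SD this needs ρ of about 0.48 or more.
- *The change comparison is biased by regression to the mean.* Under 1:1 randomisation it is unbiased; it is only less precise.
- *Every outcome has a baseline value.* Match impact counts have none, and Table 1 does not list the tackle task, GFAP or UCHL1 at baseline, although sections 2.1 and 2.2.2 cover biomechanical and blood baselines in general terms.

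**Conclusion.** The point holds as a conditional loss of precision. If the two groups are compared on change from baseline, that comparison is less precise than a baseline-adjusted one for every ρ below 1.

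On the post-match SD, the gain at 20 per group runs from about 18 percentage points at ρ = 0.3 to about 1 at ρ = 0.8. On the change SD, it runs from about 17 points (86.3% against 69.3%) at ρ = 0.3 to between 4 and 5 (73.8% against 69.3%) at ρ = 0.8. These figures rest on an assumed ρ, equal SDs at baseline and post-match, and a single post-match session.

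This is an improvement the sponsor should make because it needs nothing beyond data already planned. It is not an error that invalidates the analysis. The one-sided sizing should be dealt with as a separate matter.

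**What to change.** In section 2.5, state one of the following for the blood, biomechanical and cognitive-motor outcomes measured at baseline:

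- the comparison of sport-event and control groups at each post-match session is estimated with that outcome's own baseline value as a covariate, together with a baseline-by-session term; or
- all sessions, baseline included, are outcomes in a mixed model that constrains the two groups to a common baseline mean and estimates the group difference at each post-match session.

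Keep the demographic covariates to a few named in advance, since 40 players cannot support many.

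The cost is one sentence of analysis text and a few degrees of freedom. In the first option, the baseline covariate takes one parameter. With six post-match sessions (after each of three games, then 24, 48 and 72 h), the baseline-by-session term adds about five more. No new data, visits or players are needed.

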We expect a decline in coordination, cognitive-motor tasks, and whole-body mobility, owing to exhaustion and/or concussions, as the number of games increases. Concussive events and injuries will be assessed using a notational analysis recorded during each match. Specifically, a reduction in the performance variable associated with the mBESS stance and finger-to-nose task is expected. In the analysis of the emergent coordinative structures of the passing task, we expect to show a shift to a critical level, before which the outcome variable of passing accuracy will be maintained. Past this critical point, the self-organization of the biological structures will be unable to remain stable, and the coordination variability will rise above the functional level. Examining the structure and timing of these movement characteristics will allow us to link the dynamics to the evolving rugby games. Cognitive function tests, including the Pegboard, Tapping Task, Stroop word test, and reaction time task, are expected to display a reduction in outcomes in the repeated testing sessions as a result of fatigue and/or a concussive event. With respect to the blood-based biomarkers, we expect CK, cardiac troponin T, NSE, S100B, BDNF, GFAP, and UCHL1 to increase after a rugby match, as exercise and contact sports have been shown to cause these biomarkers to increase [8,9,10,11,12,13,14,15,16,17,18,19,20,21,22,23,24,25,26,27,28,35,37,44,45,46,47,48,49]. However, cortisol concentrations may not increase, as cortisol has been shown not to increase after American football play in the absence of brain injury [10,37]. Some variations in biomarker concentrations in the blood are expected to correspond to changes in biomechanical and cognitive-motor activities. In the examination of the interaction of whole-body movement, coordination testing, cognitive-motor tasks, and blood-based biomarkers, we expect to observe those variables most related to changes in the testing session and the other outcome variables, including the accuracy of passing.

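### Holm's step-down procedure could replace the Bonferroni procedure for post hoc session comparisons: same familywise error, never fewer rejections, and a modest power gain when several sessions are affected

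*Protocol article*

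**What the plan says.** Section 2.5 (Statistical Analysis) plans generalized linear mixed models to compare baseline with the testing days for each outcome, adjusted for demographic covariates. It then states: "Post hoc tests will be performed using the Bonferroni procedure, Mann-Whitney U test, and Chi-square test for different types of data". The significance level is worded as 95%, two-tailed, which I read as a two-sided alpha of 0.05.

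Section 2.1 fixes when players are tested after baseline: "performed immediately after each game and three times after the third game at 24, 48, and 72 h". That makes six post-baseline sessions. Section 2.5, describing the parametric mapping of continuous data, counts four sessions against baseline. The article does not say which comparisons form the Bonferroni family.

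On expected effects, section 3 (Discussion) says: "We expect a decline in coordination, cognitive-motor tasks, and whole-body mobility, owing to exhaustion and/or concussions, as the number of games increases". It also expects most of the blood biomarkers to rise after play.

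**The concern.** Without further qualification, the Bonferroni procedure means the single-step rule: every comparison in a family of m is judged at 0.05/m, however many of the others have already been rejected. Holm's rule starts at the same threshold but relaxes it after each rejection. It gives the same strong familywise control without any assumption about dependence between sessions.

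The difference shows when several sessions in one outcome are truly affected, and the hypotheses make that plausible for at least some outcomes. The first aim, in the Introduction, is change across the tournament up to 72 h, so the pattern over sessions matters as well as whether any session differs. What is at stake is some power for the second and later sessions within an outcome.

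**Working it through.** **Inputs from the article.** Two-sided alpha 0.05 (section 2.5). Planning effect: "we aimed to achieve a substantial effect size of 0.8 (Cohen’s d) on blood biomarkers" (section 2.1). Sample size: "With an alpha of 0.05 and a power of 80%, 40 participants (20 participants per group) are required" (section 2.1). Six post-baseline sessions (section 2.1).

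**Inputs assumed.** One family of six session comparisons per outcome (four as an alternative), each a comparison of the sport-event group with the control group by t-test; equal effects at the affected sessions; within-player correlation 0.5.

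**The plan's own figure.** The article gives no power for post hoc tests. Its only power figure is N = 40. With n = 2(z_α + z_β)²/d² per group:
- one-sided 0.05: 2(1.645 + 0.842)²/0.64 = 19.3, so 20 per group, N = 40 (reproduced);
- two-sided 0.05: 2(1.960 + 0.842)²/0.64 = 24.5, so 25 per group, N = 50 (not reproduced).

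That mismatch is a separate matter and does not bear on this point. Only n = 20 per arm and d = 0.8 are used below.

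**Thresholds for m = 6.**
- Bonferroni: 0.05/6 = 0.0083 for all six tests.
- Holm, from the smallest p-value upwards, stopping at the first failure: 0.0083, 0.0100, 0.0125, 0.0167, 0.025, 0.05.

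Two facts follow without simulation. Every Holm threshold is at least 0.0083, so Holm rejects whatever Bonferroni rejects. The first thresholds are equal, so if Bonferroni rejects nothing, Holm rejects nothing. Holm can therefore add at most 6 − 1 = 5 rejections, and the chance of at least one rejection is the same under both.

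**Closed-form power for one session.** Noncentrality = d√(n/2) = 0.8 × √10 = 2.530, with 38 degrees of freedom.
- At 0.0083: critical t = 2.783, power 41.1%. This is Bonferroni's per-session power.
- At 0.05: critical t = 2.024, power 69.3%. No step of Holm is more lenient, so this is a ceiling on its per-session power.
- At 0.05/4 = 0.0125 (family of four): critical t = 2.622, power 47.1%.

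**Simulation** (20,000 trials per row, d = 0.8, correlation 0.5):

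| Family | Sessions truly affected | Average per-session power, Bonferroni | Holm | Extra true sessions per outcome |
|---|---|---|---|---|
| 6 | 6 | 41.0% | 50.5% | 0.57 |
| 6 | 3 | about 42% | about 44% | 0.08 |
| 6 | 1 | 42% | 42% | under 0.01 |
| 4 | 4 | 47% | 56% | 0.37 |

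The last column is the power gain times the number of affected sessions; in the first row, 6 × (0.505 − 0.410) = 0.57. In that row the chance of at least one detection is about 80% under both rules, and the chance of detecting all six is 8.4% against 27.4%. With no true effects the familywise error is about 4% for both.

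**Sensitivity.** With all six affected at d = 0.8, correlation 0 gives 41.2% against 50.1%, and correlation 0.7 gives about 41% against 50.5%. Across d = 0.5 to 1.2, correlation 0 or 0.5, and one to six affected sessions, the largest average gain was 0.64 sessions per outcome.

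**The case against.** The strongest reply is that nothing here is wrong. Bonferroni is valid and conventional, it controls the error it is meant to control, and it contradicts nothing else in the article. That stands, and it is why the change is optional.

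Bonferroni also has an advantage of its own: simple simultaneous intervals that agree with its p-values. It would be unfair to say that the plan gives up power for nothing.

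The size depends on inferences. Section 2.5 does not define the family, and a condensed article may leave that to a fuller document. The simulated contrast is group against group by t-test, whereas section 2.5 describes baseline-to-session differences from mixed models with covariates. The percentages therefore illustrate the gap between the two rules and do not forecast this trial's power. The ordering of the two rules does not depend on any of this.

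The six-of-six pattern favours Holm most, and the article does not predict it for every outcome. The Discussion expects passing accuracy to hold up to a critical point and says that cortisol may not rise. No effect is specified separately at 24, 48 or 72 h.

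A reader might infer that up to six real session effects per outcome would be lost. That cannot happen relative to Holm: the maximum is five, and the average is below one. A reader might also infer that the reported time course would be cut short. That requires a non-significant session to be read as no effect, which the article does not propose.

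**Conclusion.** The point holds as a cheap, optional improvement in efficiency. Holm's dominance over Bonferroni at the same familywise level is a mathematical fact and needs no assumption about this trial.

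The size is conditional on the assumed family, the equal effects of d = 0.8 and the correlation of 0.5. On those terms the gain in average per-session power is about 9 to 10 points when every session in the family is affected, 2 to 3 points when three of six are, and nil when one is. The documents do not support a claim that the planned error control is faulty, that results would be biased, or that an outcome with any detectable session would be missed altogether because of this choice.

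**What to change.** In section 2.5, replace the reference to the Bonferroni procedure with the Holm step-down (sequential Bonferroni) procedure, applied to the set of session comparisons within each outcome. That wording also states what the family is.

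The cost is one phrase, with no extra participants, measurements or familywise error above the nominal 5%. Because Holm has no simple matching simultaneous intervals, Bonferroni or unadjusted intervals would be reported beside the Holm p-values and labelled as such. An interval and its p-value may then occasionally disagree. If matching intervals matter more to the investigators than the extra power, keeping Bonferroni is defensible.
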